The specific aims of the study will be: a) to assess the impact of infections—both with and without systemic inflammatory response—on frailty profiles from pre-admission to hospital discharge in older patients with no to mild pre-admission frailty (*primary aim*); b) to examine the link between changes in frailty and genetic/epigenetic markers, such as global DNA methylation and telomere length, exploring whether these biomarkers can predict the course of in-hospital and post-discharge frailty; c) to evaluate the trend of circulating inflammatory and aging-related biomarkers in modulating the impact of infections on frailty progression; and d) to assess the impact of infections on frailty trajectories over a three-month follow-up after discharge, and the modifying role of sociodemographic, clinical and (epi)genetic factors.

While previous research has linked hospitalizations to a decline in physical and cognitive health, leading to frailty in older patients, limited evidence exists on how infections specifically drive these changes. We hypothesize that patients experiencing a higher number and severity of acute infections, especially those with underlying systemic inflammation, may show a steeper functional decline during and after hospitalization. Additionally, we expect that genetic, epigenetic, and clinical factors—such as older age, multimorbidity, polypharmacy, specific DNA methylation and telomere length patterns—may modify the progression of frailty in response to infections.

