## Methods/design

### Study design and participants

The INFRAGEN study is a prospective, observational multicenter study involving the Acute Geriatric Units of four Italian centers: S. Anna University Hospital in Ferrara (Emilia-Romagna region, Italy), Padua University Hospital (Veneto region, Italy), IRCCS Foundation San Gerardo dei Tintori in Monza (Lombardy region, Italy), and Federico II University Hospital (Campania region, Italy).

Participants will be selected based on the following criteria: age ≥ 70 years, non-frailty or mild frailty status before admission (CFS < 6), and confirmed diagnosis of acute infectious diseases at the time of hospital admission or during the hospital stay, according to specific ICD-9 codes, with or without a systemic inflammatory response.

Terminally ill patients with an estimated life expectancy of less than 3 months, those with moderate to severe frailty, and individuals who do not wish to participate in the study or complete follow-up assessments will be excluded.

Written informed consent will be obtained from all participants.

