### Statistical analysis

The baseline characteristics of the study participants will be described using count and proportion for the categorical variables and mean and standard deviation, or median and interquartile ranges, for the quantitative variables, according to their distribution. These characteristics will be compared between participants by type of infection and the presence of systemic inflammatory response through the ANOVA, Student t-test, Kruskal Wallis test, or Chi-squared test, as appropriate.

The intra-individual change in FI between the pre-admission status and the patient’s condition at hospital discharge will be evaluated through the Student t-test for paired samples and then with linear mixed models. The latter analysis will be set with a random intercept and slope and adjusted for potential confounders in the association between infectious diseases and frailty changes, e.g., sociodemographic information, study center, comorbidities, length of hospital stay, and in-hospital clinical events (unrelated to the infection). The mean adjusted change in FI between pre-admission status and hospital discharge will be expressed as ß coefficient and 95% confidence interval (95% CI). Moreover, we will test whether the presence of systemic inflammation will modify the average intra-hospital change in FI. As secondary analyses, we will investigate which infection-related characteristics will be associated with higher in-hospital mortality (through the Kaplan-Mayer method and Cox regression analysis), longer hospital stay (with linear regressions), and discharge setting (with multinomial logistic regression).

The impact of infectious diseases (distinguished by number, site and severity) on frailty changes will be analyzed with linear mixed models, considering the beta coefficients (95% CI) for the interaction infection*time. Additional analyses will be performed to test whether sociodemographic, functional, clinical, and genetic/epigenetic factors interact with infectious diseases to influence the course of frailty over time.

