First, the study will quantify the impact of infections on the change in individuals’ frailty status from pre-admission to hospital discharge. Evidence from the SARS-CoV-2 pandemic suggests that infectious diseases can substantially promote frailty development even beyond 3 months of acute illness [7, 8]. However, data on how the most common types of infection, their severity, the occurrence of multiple infectious diseases, and their related level of systemic inflammation may influence the progression of frailty in older adults are lacking. Furthermore, there is some heterogeneity in the definitions of frailty adopted across various studies. Second, the project will explore the interaction between infections and in-hospital frailty status in influencing adverse endpoints, such as in-hospital mortality, length of hospital stay, and discharge destination. For instance, sepsis in frail patients has been shown to worsen mortality compared to non-frail patients [31], and other infections such as pneumonia, COVID-19, or influenza may have similar detrimental impacts [32–34]. Additionally, frailty is linked to a higher risk of urinary tract infections [35]. Third, the project will assess whether global DNA methylation and telomere length patterns at hospital admission are predictors of in-hospital and post-discharge frailty trajectories. In the literature, these epigenomic and genomic markers have been linked to cellular senescence and aging [36]. For example, shorter LTL have been associated with increased risk of infections, various malignant tumors (esophageal cancer, lymphoid and myeloid leukemia), and mortality from cardiovascular, respiratory, digestive, and musculoskeletal diseases and COVID-19 [11]. However, the role of these genomic markers in predicting frailty or functional changes has not been fully investigated [13]. This project will allow us to explore whether DNA methylation and telomere length variations are involved in the pathogenetic processes leading to frailty, especially following an infection. Notably, epigenetic modifications and telomere attrition (dynamic epigenomics) are sensitive to exogenous and endogenous stressors, which strongly relates to an individual’s baseline epigenome and their personal response to stressors, thus accounting for the relationship between epigenomic patterning and developmental trajectories or disease [37]. Although a 3-month period may be a short time interval to detect changes in LTL, we cannot rule a negative impact of infectious diseases and inflammatory processes on this aspect in vulnerable individuals, such as older inpatients. Moreover, blood cells composition of the included participants is expected to change between in-hospital and post-discharge assessments, and this issue may further influence LTL.

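### Total length of stay is adjusted for as a confounder of the infection–frailty association, although the same section analyses it as an outcome of infection

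*Protocol article*

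**What the plan says.** The primary aim, stated in the Background, is the impact of infections "on frailty profiles from pre-admission to hospital discharge in older patients with no to mild pre-admission frailty". Every participant has an infection; eligibility requires a "confirmed diagnosis of acute infectious diseases at the time of hospital admission or during the hospital stay".

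Under Statistical analysis, the change from pre-admission to discharge is tested with a paired t-test and then with linear mixed models "adjusted for potential confounders in the association between infectious diseases and frailty changes". The examples given are "e.g., sociodemographic information, study center, comorbidities, length of hospital stay, and in-hospital clinical events (unrelated to the infection"). The result is reported as follows: "The mean adjusted change in FI between pre-admission status and hospital discharge will be expressed as ß coefficient". The same paragraph tests whether systemic inflammation modifies the change. It then lists secondary analyses of which infection characteristics are associated with, among other outcomes, "longer hospital stay (with linear regressions), and discharge setting (with multinomial logistic regression").

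The next paragraph studies number, site and severity of infection, "considering the beta coefficients (95% CI) for the interaction infection*time", and names no covariates of its own. The Discussion describes infections and in-hospital frailty as jointly influencing "adverse endpoints, such as in-hospital mortality, length of hospital stay, and discharge destination".

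**The concern.** A confounder of the effect of infection on frailty must not itself be a result of the infection. For a patient admitted with an infection, total stay is known only at discharge, about when the second FI is measured. The protocol's own analyses treat it as a possible consequence of infection characteristics.

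The article also supplies the other links. The Background says hospitalisation is tied to functional decline and that infection worsens the harm done by hospitalisation, which makes stay a plausible mediator. The Discussion links frailty itself to length of stay, so stay may also share causes with the FI change, which makes it a plausible collider.

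At stake are the contrasts that carry the infection question. Because nobody in the study is uninfected, these are the comparisons by systemic inflammation, severity, number and site. If stay is allowed to act on the change, they no longer estimate the total effect of infection.

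**Working it through.** The plan gives no figure for this adjustment, so there is none to reproduce. The planning values (340 participants, 0.03 FI points) do not enter: 0.03 is a pre-to-post change, not a contrast between infection types.

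**1. The statements side by side**

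| Place | Role given to length of stay |
|---|---|
| Statistical analysis, FI-change model | confounder to adjust for |
| Statistical analysis, secondary analyses | outcome of infection characteristics |
| Discussion | adverse endpoint |

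For infections present at admission, the first role does not fit with the other two.

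**2. What the adjustment does if stay acts on the change.** All inputs here are assumptions, because the documents give none. In standardised units, let severity affect stay by *a*, stay affect FI change by *b*, and severity affect FI change directly by *c* = 0.02. Let an unmeasured factor have loading *u* on stay and effect 0.03*u* on FI change.

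- Total effect = *c* + *ab*
- Stay-adjusted effect = *c* − *a* × 0.03*u*² / (1 − *a*²)

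| *a* | *b* | Total | Adjusted, *u* = 0 | Adjusted, *u* = 0.4 |
|---|---|---|---|---|
| 0.2 | 0.01 | 0.022 | 0.020 (9% lost) | 0.019 (14% lost) |
| 0.5 | 0.02 | 0.030 | 0.020 (33% lost) | 0.017 (44% lost) |

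Last row, *u* = 0.4: 0.03 × 0.16 = 0.0048; 0.0048 / 0.75 = 0.0064; 0.5 × 0.0064 = 0.0032; 0.020 − 0.0032 = 0.0168. Simulation with 400,000 patients agreed (0.0199 and 0.0168 for that row). Intermediate inputs fell between these rows.

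**3. Sensitivity to the spread of stay.** In days, assume severe infection adds 4 days, each day adds 0.0025 FI, and the direct effect is 0.020. The total is 0.020 + 4 × 0.0025 = 0.030. Let unmeasured low reserve add 3 days and 0.03 FI per SD, and let *s* be the residual SD of stay in days. The stay coefficient is then 0.0025 + 0.09/(9 + *s*²), and the adjusted severity effect is

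0.030 − 4 × [0.0025 + 0.09/(9 + *s*²)] = 0.020 − 0.36/(9 + *s*²).

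- *s* = 4: 0.020 − 0.0144 = 0.0056 (81% lost)
- *s* = 8: 0.020 − 0.0049 = 0.0151 (50% lost)
- *s* = 12: 0.020 − 0.0024 = 0.0176 (41% lost)

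If the unmeasured factor lengthens stay but lowers FI at discharge by the same amount, the sign flips. At *s* = 4 the adjusted effect is then 0.020 + 0.0144 = 0.0344, above the total of 0.030. So the direction is not fixed either.

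**4. Dependence on model form.** Mixed models with a random intercept were fitted to 2,000 simulated patients with two complete time points (*a* = 0.5, *b* = 0.02, *c* = 0.02, *u* = 0).

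| Model | time | severity × time |
|---|---|---|
| without stay | 0.0282 | 0.030 |
| stay as main effect | 0.0282 | 0.030 |
| stay × time | 0.0283 | 0.020 |

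A time-constant covariate shifts both measurements of a person equally and cancels from the change. Only the interaction with time alters the contrast. With stay centred, as here, the mean change hardly moves even then.

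**The case against.** The strongest reply has four parts.

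- **In-hospital events.** A reader might infer that the listed events are mediators too, since many occur after infection onset. The text limits them to events unrelated to the infection, so as defined they lie off that pathway. This stands. What remains is only that calling an event unrelated is a judgement made after onset.
- **Hospital-acquired infection.** A reader might infer that stay can never be a confounder here. Infections may arise during the stay, and the number of infections is an exposure. Time already spent in hospital can both raise the chance of infection and worsen frailty. This stands: the fault lies in using total stay rather than stay before onset.
- **Model form.** The article does not say whether stay is interacted with time, and a main effect alone leaves the estimates unchanged. The covariate list is also attached to the pre-admission-to-discharge model, introduced as examples, and preceded by an unadjusted paired test. All this stands against saying that the estimate is biased. It does not rescue the wording: control of confounding of frailty changes either acts on the change and can remove part of the effect, or does not act on it and controls nothing.
- **Target of estimation.** The Background asks how infections specifically drive decline, so separating infection from hospitalisation is a legitimate question. That is a mediation question, however, and the plan presents the adjustment as control of confounding.

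**Conclusion.** The point holds for total length of stay and for infections present at admission. There the plan treats one variable both as a confounder and as an outcome of infection. Adjusting the FI change for it may remove the part of the total effect that acts through a longer stay, and may open a collider path.

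The losses of 9% to 44% rest wholly on assumed inputs and on stay acting on the change. A reader might infer from the 81% case that most of the effect would vanish. That figure needs a residual SD of stay of about 4 days, which the documents do not give; at 8 or 12 days the same inputs give 50% or 41%. Nor do the documents show that the planned estimate is biased: the model form is not stated, and size and direction cannot be derived from them.

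**What to change.** Remove total length of stay from the main adjustment set. Adjust only for covariates fixed before infection onset: sociodemographic factors, centre, comorbidities and pre-admission function, plus stay before onset for hospital-acquired infections. State that the same rule applies to the models for systemic inflammation and for number, site and severity of infection. Report the model adjusted for total stay only as a labelled sensitivity or mediation analysis. In-hospital events unrelated to the infection need not be deleted as mediators.

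The cost is a change of wording, plus infection-onset dates for hospital-acquired cases if these are not already recorded. No new visits are needed. The small downside is that the main estimate then includes whatever a longer stay contributes, and the text should say so.

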### Study procedures

Data will be collected using the RedCap platform. The study will include three assessment points (Fig. 1): hospital admission (Time 1), discharge (Time 2), and three months after hospital discharge (Time 3).

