**Fig. 1 Fig1:**
[figure not shown]
Graphical summary of the INFRAGEN study protocol

Time 3 assessment will be performed through an outpatient follow-up visit, home visit, or telephone interview, depending on the centers’ resources and the patient’s characteristics and availability.

Each assessment will include face-to-face interviews, administration of validated scales and questionnaires, physical tests, and blood sampling (the latter only at Time 1 and 3, and limited to the subgroup undergoing outpatient clinic visits).

The data collected from each participant are briefly described below.

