
Finally, the INFRAGEN project will clarify which inflammatory markers (e.g., Interleukins 1 to 18, GDF15, IF1, TNFR, MCP-1) are mostly predictive of frailty progression and adverse health-related outcomes in older adults with acute infections. Frail individuals are known to have significantly reduced innate immune function, T-cell activity, antibody production, and a persistent state of chronic mild inflammation. However, longitudinal studies have not demonstrated a clear association between higher inflammatory levels and the onset of frailty [4]. Research in this field may help contribute to the current literature on the relationship between inflammatory markers, frailty pathophysiological pathways, and patient clinical phenotypes. By enrolling patients with no or only mild frailty before hospital admission and who are affected by acute infections generally triggering inflammation, we will be able to derive a risk stratification of frailty development based on inflammatory, genetic/epigenetic and clinical factors.

The INFRAGEN project has several strengths, including multicenter patient enrollment, standardization of biochemical and genomic analyses in a central laboratory, and broad multidomain characterization of older patients. Moreover, combining clinical and pre-clinical research expertise will allow us to provide novel findings that will contribute to the pathophysiological understanding of frailty and may have concrete implications for clinical practice. Potential critical points may include the recruitment of patients with no or mild frailty in acute geriatric units, which may be challenging because older adults needing hospitalization are often clinically complex and frail at the time of admission. However, the coordination of participating centers may transform these potential challenges into opportunities to investigate understudied topics. Another limitation of our study is the relative homogeneity of the older Italian population, which is still predominantly Caucasic and may make our results not generalizable to other ethnic groups. The generalizability of the project findings may also be affected by the involvement of only Italian Geriatric units. However, these wards exhibit some differences in terms of hospital organization, infection epidemiology, and regional healthcare practices, which partly account for the heterogeneity of healthcare systems.

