## Conclusions

The INFRAGEN study will contribute to understanding the role of infections and inflammation in prompting the development of frailty in older adults. Additionally, it will explore whether genetic and epigenetic factors, such as global DNA methylation and telomere attrition, may modify the impact of infections on frailty trajectories during hospitalization and after hospital discharge. Therefore, the results of this project will help clarify the underlying pathophysiological mechanisms of frailty and stratify the risk of frailty and other adverse outcomes (e.g. mortality, prolonged hospital stay, repeated hospital readmissions, infection recurrence, or reduced independence) in older inpatients with acute infections.

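### The mortality analysis ends at discharge although a three-month contact is planned for all survivors; add all-cause death within 90 days as a fixed-window endpoint

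*Protocol article*

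**What the plan says.** Among the secondary analyses, the Statistical analysis section asks "which infection-related characteristics will be associated with higher in-hospital mortality" ("through the Kaplan-Mayer method and Cox regression analysis"). The same sentence examines infection characteristics in relation to longer hospital stay and to discharge setting. The Discussion names the same three outcomes and again limits mortality to the hospital episode. Mortality appears in none of the four stated aims.

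Study procedures sets three assessment points, the last of them three months after discharge. The text below Fig. 1 says: "Time 3 assessment will be performed through an outpatient follow-up visit, home visit, or telephone interview". Only the blood sample is confined to the outpatient subgroup, so some form of contact is planned for all survivors. People unwilling to complete follow-up are excluded at entry.

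The Conclusions say the results will help "stratify the risk of frailty and other adverse outcomes" and list mortality among those outcomes, without an in-hospital limit. On the centres, the Discussion says "these wards exhibit some differences in terms of hospital organization" and goes on to infection epidemiology and regional practice.

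**The concern.** An in-hospital death endpoint has no fixed length. It closes on the day the ward discharges the patient, and that day depends on recovery, bed pressure, local step-down capacity and regional habit. Two patients with the same infection and the same date of death are classed differently if one was transferred out earlier.

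This matters for the hazard ratios of number, site and severity of infection because the plan itself treats those characteristics as possible determinants of length of stay and discharge setting. If they do affect when patients leave, the exposure helps decide who remains under observation, and those still in the ward are a selected group. The estimate then mixes the effect on dying with the effect on being discharged.

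The contact needed to avoid this is already planned. No analysis described in the article covers death after discharge, so early post-discharge deaths do not enter the mortality stratification that the Conclusions describe in general terms.

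**Working it through.** **1. The plan's own figure.** The sample size of 340 is for a Frailty Index change of 0.03 and has no bearing on mortality. The SD is not given in the article, so 340 cannot be reproduced forward. Solved backwards for a paired comparison, it implies an SD of 0.03 × √340 / 2.80 ≈ 0.197. No event count, mortality rate or power is stated for the mortality analysis. I use 340 only as the denominator.

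**2. Does the planned contact cover 90 days?** Time 3 is three months after discharge. Admission, and diagnosis of a hospital-onset infection, both come before discharge. Ninety days from either therefore ends at or before Time 3 for essentially every patient discharged alive. A 90-day window from admission can lose only in-hospital deaths after day 90, which should be rare, and it adds all earlier deaths after discharge.

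**3. Does the in-hospital window depend on exposure and ward?**
- Exposure: the sentence in Statistical analysis that sets up the mortality analysis also tests infection characteristics against length of stay and discharge setting.
- Ward: the Discussion states that the wards differ in organization and regional practice.
- Live discharge: if it is treated as censoring in Kaplan-Meier or Cox, the censoring is likely to be informative. Treating it as a competing event repairs the estimator, but the endpoint still closes at discharge.

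**4. Illustrative size.** All mortality risks below are assumptions: 5-8% in hospital and 15-20% at 90 days, with 10% added as a higher in-hospital value. Deaths d = 340 × risk.

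For one continuous factor with hazard ratio (HR) 1.5 per SD, two-sided alpha 0.05:
- power = Φ(ln 1.5 × √d − 1.96)
- HR detectable with 80% power = exp(2.80/√d)

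For a binary factor split 50:50 with HR 2: power = Φ(ln 2 × √(d/4) − 1.96).

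| Assumed risk | Deaths among 340 | Power, HR 1.5 per SD | Detectable HR per SD | Power, HR 2, 50:50 |
|---|---|---|---|---|
| 5% | 17 | 39% | 1.97 | 30% |
| 8% | 27 | 56% | 1.71 | 44% |
| 10% | 34 | 66% | 1.62 | 52% |
| 15% | 51 | 83% | 1.48 | 70% |
| 20% | 68 | 92% | 1.40 | 82% |

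Example for d = 17: 0.405 × 4.123 − 1.96 = −0.29, and Φ(−0.29) ≈ 0.39.

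HR 2 with 80% power needs 4 × 2.80² / (ln 2)² = 65.3, so 66 deaths, or 66/340 ≈ 19%.

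**5. Sensitivity.** The table uses the same HR in both windows. If the effect of an acute infection weakens after discharge and the 90-day HR is 1.3 per SD (assumption), 51 and 68 deaths give Φ(0.262 × 7.141 − 1.96) ≈ 47% and Φ(0.262 × 8.246 − 1.96) ≈ 58%. That is close to the 39-56% for in-hospital death at HR 1.5. If in-hospital risk were itself 15%, power would already be 83%.

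**The case against.** The in-hospital endpoint is deliberate and consistent. Methods and Discussion name the same three hospital-episode outcomes, and mortality is not among the aims. The phrase in the Conclusions is a closing remark that gives mortality as one example, and in-hospital mortality falls within that word. The article is condensed, so post-discharge outcomes may be handled in a fuller document. Vital status is not named as a Time 3 item, and the mode of contact varies with centre resources, so a longer window could exchange dependence on discharge for centre-dependent ascertainment. The analysis compares infection characteristics, not centres, so discharge practice biases the hazard ratios only if it is related to those characteristics.

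Much of this stands, and it rules out three stronger readings that a reader might infer:
- *That the plan cannot stratify mortality risk.* It can, for in-hospital death. The mismatch is only with the unrestricted wording of the Conclusions.
- *That in-hospital deaths will be too few.* The exclusions (CFS 6 or above; "Terminally ill patients with an estimated life expectancy of less than 3 months") make a low risk plausible, but the article gives no rate. The life-expectancy criterion also bears on deaths within three months.
- *That in-hospital death should become merely descriptive.* It is the better ascertained of the two endpoints, and nothing in the document argues for dropping its model.

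The last objection, that a link to infection characteristics is needed, is met by the plan's own decision to test those characteristics against length of stay and discharge setting. The ascertainment objection is a real cost and is carried into the fix.

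**Conclusion.** The point holds as an inexpensive improvement to a secondary analysis; the primary aim is unaffected. The article fixes a mortality window that closes at discharge, plans a later contact with all survivors, and describes no analysis of death after discharge. The in-hospital hazard ratios therefore partly reflect discharge timing and destination, to an extent that the document does not allow one to quantify.

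A fixed window reduces that dependence whatever the mortality rate, and it should add deaths. How many is unknown: the contrast of 17-27 with 51-68 deaths rests on assumed risks, and the power gain also assumes an equal hazard ratio in both windows. The case for the change rests on the definition of the window. The power figures are only illustrative.

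**What to change.** - Add all-cause death within 90 days of admission as the main mortality endpoint for the Cox models of infection characteristics. For hospital-onset infection, count the 90 days from diagnosis.
- Record vital status and date of death at the Time 3 contact, from a proxy if the patient cannot be reached. Censor those lost at last contact and report ascertainment by centre.
- Keep the in-hospital mortality analysis alongside it, with discharge alive as a competing event.
- If the endpoint is not added, limit the Conclusions to in-hospital mortality.

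The cost is two data fields at a contact already planned and some analysis wording. The downside is that some patients will be lost before Time 3 and that completeness may differ between centres, which is why it should be reported by centre.

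### Secondary analyses: Kaplan-Meier with censoring at discharge alive overstates in-hospital mortality, and linear regression of length of stay is biased by in-hospital death

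*Protocol article*

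**What the plan says.** The Statistical analysis section of the protocol article sets out the secondary work as follows: "As secondary analyses, we will investigate which infection-related characteristics will be associated with" three outcomes, each with its own method. They are "higher in-hospital mortality (through the Kaplan-Mayer method and Cox regression analysis), longer hospital stay (with linear regressions"), and "discharge setting (with multinomial logistic regression").

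Discharge is therefore an outcome in its own model, but it is not named as a competing event in the mortality analysis. The article gives no cumulative incidence method and no fixed time horizon. It does not say how patients discharged alive are censored, or whether patients who die enter the length-of-stay regression.

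The assessment points in Study procedures are "hospital admission (Time 1), discharge (Time 2), and three months after hospital discharge (Time 3"), so the in-hospital phase ends at discharge. The Discussion lists the same endpoints ("such as in-hospital mortality, length of hospital stay, and discharge destination") under the second of the study's four stated contributions, without adding methods.

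**The concern.** A patient who goes home alive can no longer die during that stay. Kaplan-Meier with censoring at discharge treats such a patient as still exposed to the daily risk of in-hospital death of those who remain. The curve then describes a hypothetical ward that nobody leaves alive, and its level is too high as an estimate of the proportion dying in hospital.

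The comparison between infection groups can also mislead. If a characteristic delays discharge, patients spend more days at risk and more of them die in hospital, even when the daily death rate is unchanged. Neither the Kaplan-Meier curves nor the Cox hazard ratio shows this.

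Length of stay has the related problem that a stay can end in recovery or in death. A linear regression on days in hospital does not separate the two.

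At stake are the reported mortality curves by infection type and severity, and the estimated link between severity and stay. The Conclusions say that the results will help to stratify the risk of both mortality and prolonged stay.

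**Working it through.** **Inputs.** The article gives no in-hospital mortality, no length of stay and no figure for these analyses, so there is nothing of the plan's own to reproduce. Its one computed design figure, at least 340 participants, concerns the Frailty Index and plays no part here. All rates below are assumptions.

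**1. Level of the mortality curve.** Let m be the daily hazard of in-hospital death and d the daily hazard of discharge alive, both constant.

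- True cumulative incidence at day t: m/(m+d) × (1 − exp(−(m+d)t))
- One minus Kaplan-Meier, censoring at discharge: 1 − exp(−mt)

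For d = 0.10 and m = 0.008, at day 10: 0.008/0.108 × (1 − exp(−1.08)) = 4.9%, against 1 − exp(−0.08) = 7.7%. At day 30: 0.008/0.108 × (1 − exp(−3.24)) = 7.1%, against 1 − exp(−0.24) = 21.3%.

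| d | m | Day | True risk | 1 − KM |
|---|---|---|---|---|
| 0.10 | 0.008 | 7 | 3.9% | 5.4% |
| 0.10 | 0.008 | 10 | 4.9% | 7.7% |
| 0.10 | 0.008 | 30 | 7.1% | 21.3% |
| 0.08 | 0.005 | 30 | 5.4% | 13.9% |
| 0.12 | 0.010 | 30 | 7.5% | 25.9% |

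Across 5–15% in-hospital deaths and mean stays of 8–12 days, 1 − KM at day 30 is 11.8–43.0%, against a true 4.6–14.6%. Taken scenario by scenario, that is 2.3 to 3.5 times too high.

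The result does not depend on constant discharge hazards. With gamma-distributed times to discharge (mean 12 days), simulated 30-day risks of 5.3%, 10.8% and 16.2% appear as 13.2%, 25.5% and 37.2%.

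**2. What the Cox hazard ratio shows.** Take two groups with the same death hazard, 0.01 per day, and mean times to discharge of 8 and 14 days. The cause-specific hazard ratio is 1.0, and 1 − KM at day 30 is 25.9% in both. Final in-hospital mortality is 0.01/(0.01 + 1/8) = 7.4% against 0.01/(0.01 + 1/14) = 12.3%. The hazard ratio is correct for the daily rate, but it does not show the difference in mortality.

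**3. Length of stay.** Two groups were simulated with gamma times to discharge averaging 10 and 13 days, a true difference of 3.0 days in the absence of death. The first group's death hazard is 0.004 per day, and the second group's is a multiple of it.

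| Death hazard, second vs first | Deaths | Difference, deaths included | Difference, survivors only |
|---|---|---|---|
| Equal | 4% vs 5% | 2.8 days | 2.9 days |
| 5-fold | 4% vs 22% | 1.2 days | 1.9 days |
| 10-fold | 4% vs 38% | −0.3 days | 0.9 days |

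Including deaths attenuates the difference, and the sign changes only when the death hazards are very far apart. Excluding deaths leaves a smaller bias in the same direction.

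**The case against.** Several points on the other side stand.

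- **Status.** These are secondary analyses. The primary aim is change in frailty from pre-admission to discharge, analysed by paired t-test and mixed models, and mortality is not among the aims listed in the Background. A reader might infer that the main result is at risk; nothing here touches it.
- **Cox regression.** A reader might infer that the whole mortality analysis is invalid. The stated question is one of association, and Cox with censoring at discharge gives a legitimate cause-specific hazard ratio. What it lacks is a companion model for discharge alive.
- **Censoring rule.** Censoring at discharge is not written down. If discharged patients were kept at risk to a fixed horizon, with no other censoring, Kaplan-Meier would equal the cumulative incidence. Such details are often left to a fuller document. But no horizon is given, and censoring at discharge is the usual reading of an in-hospital endpoint.
- **Deaths in the stay regression.** A reader might infer that early deaths will be counted as short stays. The article neither includes nor excludes deaths, so this holds only if they are included. The survivors-only alternative is also biased, so the named method is a problem either way.
- **Size.** Day 30 is an unfavourable place to look. With hazards of 0.10 and 0.008, exp(−3.24) = 3.9% of patients remain in hospital, about 13 of 340. At days 7 to 10 the excess is 1.4- to 1.6-fold.
- **Reversal.** It is tempting to say that severe infection will appear to shorten stay. Constant hazards can produce this: 1/0.105 = 9.5 days for mild cases (discharge 0.10, death 0.005) against 1/0.11 = 9.1 days for severe cases (0.07, 0.04). That needs an 8-fold death hazard and 0.04/0.11 = 36% dying. Attenuation is the realistic expectation.

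**Conclusion.** The point holds as a recommended correction to secondary analyses. Kaplan-Meier is a stated choice of method. If patients discharged alive are censored, it overstates the in-hospital death proportion once discharges precede later deaths. The direction does not depend on the assumed rates; the size does. In the main illustration the excess is about 1.6-fold at day 10 (4.9% against 7.7%) and 3-fold at day 30 (7.1% against 21.3%). Whether comparisons between groups are also distorted depends on whether their discharge rates differ.

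The Cox model is sound as a cause-specific analysis but cannot by itself answer which characteristics raise in-hospital mortality when they also delay discharge. Linear regression of stay is biased towards a smaller difference when the group with longer stays also has more deaths. The bias is larger if deaths are included and smaller, but still present, if they are excluded.

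**What to change.** - Replace Kaplan-Meier with the Aalen-Johansen cumulative incidence of in-hospital death, with discharge alive as the competing event.
- Keep the planned Cox model, labelled as cause-specific for death, and add a companion cause-specific model for discharge alive. A Fine-Gray model is an alternative where an effect on cumulative incidence is wanted.
- Make time to discharge alive, with death as the competing event, the main length-of-stay analysis. Linear regression can stay as a supportive analysis, with the handling of deaths stated.

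The cost is analysis wording and code, slightly more work, and estimates that are less familiar to clinical readers. The planned analyses of time to in-hospital death and of stay already need the dates of admission, discharge and in-hospital death, so no new data item should be required. The sample size and the primary analysis do not change.
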